### Study design and setting

MenGO is a Phase III open-label unblinded randomised control trial of 4CMenB vaccination of GBM to protect against *N. gonorrhoeae* infection. The study design is shown in Fig. 1. Participants will be randomly assigned by 1:1 allocation to either: (1) the ‘4CMenB vaccine arm’ who will be vaccinated at baseline and 3 months with 4CMenB; or (2) the unvaccinated ‘no treatment arm’. An STI screen as per the Australian STI guidelines [28] will occur at baseline and at 3 monthly study visits over 2 years. Blood will be collected for antibody analysis at 0, 3, 6, 12, and 24-month visits, and information regarding demographics, concurrent medication, previous gonorrhoea infections, antibiotic use and sexual behaviour risks will be collected at each visit. The trial will be conducted in accordance with the guidelines for Good Clinical Practice (GCP) and will satisfy Consolidated Standards of Reporting Trials (CONSORT) reporting conventions [29].

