## Data collection and management

Data collected at each visit will include patient demographics, concurrent medication, previous *N. gonorrhoeae* infections, antibiotic use, sexual behaviour risks and previous STI and blood borne virus (BBV) testing within the last 3 months. If the participant has had testing for *N. gonorrhoeae* elsewhere, all efforts will be made to obtain a copy of those results and associated clinical information either from the patient or directly from the treating physician or clinic. If the participant reports any antibiotic use, the name of the antibiotic and reason for use will also be asked.

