Log(base2) transformed antibody, SBA, OPA and neutralisation titres for each of the 0, 3, 6, 12, and 24-month time points will be, initially, compared between vaccinated and non-vaccinated groups by linear regression with log_2_-titre at time 0 as a covariate. Other clinical and demographic covariates will also be tested, along with vaccination status. Variables will be considered as covariates and retained in the model if P < 0.05. Finally, a mixed effects analysis of the trajectory of the log_2_-titres over the 24-month duration of the study will be performed with participant number as a random effect and vaccination status as the fixed effect of interest. Again, other clinical and demographic variables will be tested as covariates.

The number and percentage of treatment-emergent AEs, study treatment-related AEs, SAEs and AEs leading to study withdrawal will be provided.

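### The titre models keep unlisted covariates by P < 0.05 and do not limit them to baseline values: little harm if all are baseline, but the adjusted vaccine effect stops being the randomised contrast if infection during follow-up is kept

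*Protocol article*

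**What the plan says.** The protocol article, Statistical methods, plans the antibody analysis in three steps.

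- **Initial comparison.** "Log(base2) transformed antibody, SBA, OPA and neutralisation titres for each of the 0, 3, 6, 12, and 24-month time points" are first compared between arms "by linear regression with log_2_-titre at time 0 as a covariate".
- **Covariate step.** "Other clinical and demographic covariates will also be tested, along with vaccination status". The retention rule follows: "Variables will be considered as covariates and retained in the model if P < 0.05".
- **Mixed model over 24 months.** "Again, other clinical and demographic variables will be tested as covariates". No retention threshold is restated here.

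The candidate variables are not named, and the text does not say whether baseline or follow-up values are meant. It also does not say whether one covariate set serves all assays and visits. Study design and setting states that "information regarding demographics, concurrent medication, previous gonorrhoea infections, antibiotic use and sexual behaviour risks will be collected at each visit", and Data collection and management repeats that these data are taken at each visit. Vaccine doses are given at baseline and month 3.

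**The concern.** This is a stated rule, so the issue is not one of missing detail: an analysis plan that follows the rule inherits it, and one that does not departs from the published protocol. It raises two separate problems.

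1. **Selection by P-value.** Covariates are chosen by their association with the outcome in the same data, and the natural reading is that this is redone for each titre, each visit and the mixed model. Ordinary standard errors take the chosen model as given, so intervals are somewhat too narrow.
2. **No limit to baseline.** Infection during follow-up is the primary outcome, the trial hypothesises that vaccination reduces it, and it is a plausible predictor of anti-gonococcal titre. If it passes P < 0.05 and stays in, the vaccine coefficient compares arms at equal infection status. That is not the comparison randomisation protects.

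The Discussion section presents the immune analysis as a possible route to a correlate of protection. That use needs a vaccine effect on titre with one clear meaning.

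**Working it through.** **No figure to reproduce.** The protocol gives no sample size, power or effect for titres. The check asks how the retention rule behaves in the stated linear model, against a model with arm and month-0 titre only.

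**Inputs from the document.** Incidence 37.8 per 100 person-years (Background); 24 months' follow-up; 30% efficacy, 112 evaluable men, a target of 130 and under 10% loss (Sample size). 130 × 0.9 = 117. Four titre types × four post-baseline visits (3, 6, 12, 24) = 16 fits, before the mixed model.

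**Assumed, not in the document.** Residual SD, size of the vaccine effect, number of candidate covariates, and any rise in titre after infection.

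**Step 1: chance retention.** With k unrelated, independent candidates, the chance that one fit keeps at least one is 1 − 0.95^k:
- k = 6: 26%
- k = 12: 46%
- k = 20: 64%

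Different fits will therefore often carry different covariates.

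**Step 2: baseline candidates only.** Assumed: vaccine effect 1 log2, SD 1.3, baseline-titre slope 0.75; 6, 12 or 20 candidates, one third with coefficient 0 or 0.3; univariate screening or backward elimination; 3,000 runs each.
- Mean estimate 0.99 to 1.02 against a true 1.0: essentially no bias.
- Coverage at N = 112: 92.5% to 94.7%. At N = 60: 91.1% to 94.5%.
- Fixed model: 94.4% to 95.3%.
- A separate null simulation (N = 117, 8 to 20 noise covariates) put type I error at 5.3% to 5.9%, against about 5.0%.

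In a randomised linear model, different baseline adjustment sets target the same mean difference, so differing sets alone do not change what is estimated.

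**Step 3: infection during follow-up as a candidate.** Two-year risk:
- Control: 1 − exp(−0.378 × 2) = 0.530
- Vaccine at 30% efficacy: 1 − exp(−0.378 × 2 × 0.7) = 0.411
- Gap: 0.120 (from unrounded risks)

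With an assumed direct effect of 0.5 log2 and boost d, the randomised difference is 0.5 − d × 0.120. When infection is retained, the coefficient moves to about 0.5. Simulated with N = 117 and SD 1.5:

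| Boost d (log2) | Randomised difference | Infection kept | Coverage of the randomised difference |
|---|---|---|---|
| 0.5 | 0.44 | 42% | 94% |
| 1 | 0.38 | 94% | 92% |
| 2 | 0.26 | 100% | 86–87% |

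The last row can be checked by hand. SE ≈ 2 × 1.5/√117 = 0.277; shift = 2 × 0.120 = 0.239 (unrounded gap); shift/SE = 0.86; coverage ≈ Φ(1.96 − 0.86) − Φ(−1.96 − 0.86) = 0.86.

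**Step 4: other assumptions.** Boosts are again 0.5, 1 and 2 log2, with N = 112, SD 1.3, direct effect 1 log2 and 4,000 runs.
- 30% v 21% infected: kept in 40%, 93% and 100% of runs; coverage 95.0%, 93.7% and 88.8%.
- 53% v 37% infected (30% read as a cut in two-year risk): coverage 94.1%, 90.4% and 75.5%.
- Fixed model in both: 95.0% to 95.6%.

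**The case against.** The strongest reply has four parts.

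- **A sound model is already planned.** Arm plus month-0 titre comes first, for every titre and visit, and the text never says the selected model replaces it. This stands. A reader might infer that chance alone decides which vaccine effect is reported; the document does not say so. What it leaves open is which result is the main one.
- **Follow-up values are not prescribed.** A reader might infer that the models will adjust for variables collected after vaccination. No section says that. The same variables are also collected at baseline, and the preceding paragraph on the Poisson model uses a similar phrase for characteristics not expected to differ under randomisation. This stands too: the fault is that the rule permits such values.
- **The large losses come from conditioning, not from selection.** At 30% efficacy with a 2 log2 boost, infection is kept in every run, so chance plays no part. Lower figures, down to 47%, can be produced by adding the 30% to 10% contrast from Sample size to a 2 log2 boost, but they stack assumptions that the document does not support.
- **Candidate lists belong in an analysis plan.** This is fair for the list itself. It does not excuse the retention rule, which the article states.

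Two further inferences fail: that effects cannot be compared across assays because covariate sets differ, and that the intervals are wrong in general. With baseline covariates neither is so (Step 2).

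**Conclusion.** The point holds in a limited form. The protocol commits to keeping unlisted covariates in the titre models by P < 0.05 and sets no baseline restriction.

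- **Baseline covariates only:** the vaccine effect keeps its meaning, and coverage is about 92.5% to 95% at about 112 men. This is a small loss from intervals that ignore selection.
- **A variable affected by vaccination is kept:** the adjusted coefficient is no longer the randomised contrast. If infection raises titre and vaccination reduces infection, it overstates that contrast. At 30% efficacy applied to the rate, coverage is about 95% down to 86% for boosts of 0.5 to 2 log2, and lower if 30% is read as a cut in two-year risk with a smaller SD.

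The second result depends on infection being used as a candidate and on an assumed boost, neither of which the document gives. The endpoint is secondary and no success criterion depends on it, so importance is low to moderate.

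**What to change.** In the titre paragraph of Statistical methods, and in the analysis plan:

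- Delete the P < 0.05 retention rule.
- Name the arm plus month-0 log2 titre model as the main comparison. If more adjustment is wanted, add a short list of baseline covariates fixed before data are seen (for example age, PrEP use at entry, gonorrhoea before entry), identical for every assay, every post-baseline visit and the mixed model.
- State that no variable measured after randomisation enters that comparison.
- Report any analysis that accounts for infection or antibiotic use during follow-up separately, as supportive.

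This takes two or three sentences and needs no new data, samples or participants. The only statistical cost is a few degrees of freedom spent on covariates that may prove unrelated to titre.

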## Discussion

A vaccine to protect against *N. gonorrhoeae* infection is urgently needed due to the rising gonorrhoea case numbers and the continued emergence of antibiotic resistance. Despite more than a century of research, only four gonococcal vaccine candidates have been tested in human clinical trials and none of these elicited protection against gonorrhoea [14]. Failures of these early vaccine candidates created hesitancy in the field and delayed gonococcal vaccine development. However, the field has been reinvigorated by recent epidemiological [17, 19, 20, 36–39] and in vitro data [40] suggesting that meningococcal B vaccines may provide cross protection against gonorrhoea.

MenGO is one of the first randomised control trials worldwide that aims to determine the efficacy of the licenced meningococcal B vaccine 4CMenB against gonorrhoea. The trial includes GBM on PrEP, or GBM with a recent *N. gonorrhoeae* infection. This study is limited to GBM due to the high gonorrhoea incidence in this cohort. In Australia, the majority of *N. gonorrhoeae* infections are in GBM [3], and GBM on PrEP have a gonorrhoea incidence of 37.8 cases per 100-person years [5]. Current guidelines for participants taking PrEP recommend 3-monthly review by a health practitioner for testing for STIs [41]. Therefore, participants are unlikely to bear an excess burden to participate in this study. Recent, prior infection with *N. gonorrhoeae* is a risk factor associated with STI diagnosis [42] and is therefore added as an inclusion criterion.

If this study shows that the 4CMenB vaccine is effective in reducing the incidence of gonorrhoea in GBM, this will be the first direct evidence that vaccination can prevent *N. gonorrhoeae*. The opportunity to use the licenced 4CMenB vaccine would be a relatively rapid and cost-effective approach to reduce gonorrhoea prevalence. Given the high gonorrhoea incidence in GBM, combined increased risk of HIV acquisition associated with concurrent *N. gonorrhoeae* infection [43, 44] and the current threats to management of gonorrhoea due to the emergence of multi-drug resistance [45] new prevention strategies are urgently needed in high risk populations such as GBM. Use of 4CMenB in GBM would also impact the wider population due to bridging between GBM and heterosexuals [46, 47]. Furthermore, outcomes of this study would aid policy and practice change to facilitate the investigation and use 4CMenB as a general population gonorrhoea prevention strategy.

The type of the immune response needed to prevent infection with *N. gonorrhoeae* is unknown, and investigation of the immune response to 4CMenB in this study will enable characterisation of antibodies that are cross-reactive with *N. gonorrhoeae.* This may enable identification of the mechanism of vaccine-mediated protection and of a correlate of immune protection. This aspect of the study is unique and of critical importance to enable ongoing evaluation of 4CMenB cross-protection and to facilitate the development of a gonorrhoea vaccine with higher efficacy and/or a different product profile if required.

If 4CMenB is effective against *N. gonorrhoeae*, this could lead to a widespread change in prevention and control strategies, which may lead to a substantial decrease in gonorrhoea. This would improve sexual and reproductive health and reduce costs associated with testing, treatment and management of *N. gonorrhoeae*-associated antimicrobial resistance and sequelae.

## Data Availability

Data sharing does not apply to this article as data collection has not yet been completed or analysed.

## List of abbreviations

4CMenB: four-component meningococcal B vaccine
ELISA: enzyme-linked immunosorbent assay
GBM: gay and bisexual men
HIV: Human immunodeficiency virus
HREC: Human Research Ethics Committee
MSM: Men who have sex with men
NAAT: Nucleic acid amplification test
OPA: Opsonophagocytic activity
PrEP: Pre-exposure prophylaxis
RCT: Randomised controlled trials
SBA: serum bactericidal activity
STI: Sexually transmissible infection.
